## Abstract

**Introduction:**

After an acute infection with the corona virus 10-20% of those affected suffer from ongoing or new symptoms. A causal therapy for the phenomenon known as Long/Post-COVID is still lacking and specific therapies addressing psychosocial needs of these patients are imperatively needed. The aim of the PsyLoCo-study is developing and piloting a psychotherapeutic manual, which addresses Long/Post-COVID-related psychosocial needs and supports in coping with persistent bodily symptoms as well as depressive or anxiety symptoms.

**Methods and analysis:**

This pilot trial implements a multi-centre, 2-arm (N=120; allocation ratio: 1:1), parallel group, randomised controlled design. The pilot trial is designed to test the feasibility and estimate the effect of 1) a 12-session psychotherapeutic intervention compared to 2) a wait-list control condition on psychosocial needs as well as bodily and affective symptoms in patients suffering from Long/Post-COVID. The intervention uses an integrative, manualized, psychotherapeutic approach. The primary study outcome is health-related quality of life. Outcome variables will be assessed at three timepoints, pre-intervention (t1), post-intervention (t2) and three months after completed intervention (t3). To determine the primary outcome, changes from t1 to t2 are examined. The analysis will be used for the planning of the RCT to test the efficacy of the developed intervention.

**Discussion:**

The pilot study will evaluate a 12-session treatment manual for Long/Post-COVID sufferers and the therapy components it contains. The analysis will provide insights into the extent to which psychotherapeutic treatment approaches improve the symptoms of Long/Post-COVID sufferers. The treatment manual is designed to be carried out by psychotherapists as well as people with basic training in psychotherapeutic techniques. This approach was chosen to enable a larger number of practitioners to provide therapeutic support for Long/Post-COVID patients. After completion of the pilot study, it is planned to follow up with a randomized controlled study and to develop a treatment guideline for general practitioners and interested specialists.

**Trial registration:**

The pilot trial has been registered with the German Clinical Trials Register (Deutsches Register Klinischer Studien; Trial-ID: DRKS00030866; URL: https://drks.de/search/de/trial/DRKS00030866) on March 7, 2023.

## Introduction

### Background and rationale

Since the first outbreak of SARS-CoV-2 in December 2019 over 766 million cases of infections with the corona virus have been officially confirmed worldwide (1). Many of those who have overcome the acute COVID-19 infection report continuing symptoms extending several weeks or months. This condition, which is characterized by new or ongoing symptoms four weeks or more after the start of acute COVID-19, is commonly referred to as Post-COVID-19 or Long-COVID (2). In the recent literature, the resulting pathological condition has also been referred to as “long COVID/post-acute COVID” and “chronic post-COVID syndrome” (3). According to the WHO an estimated 10-20% of those who had been infected with SARS-CoV-2 are suffering from Long/Post-COVID (4). However, the estimates span between 2.3% and 72.5% (5, 6).

Like other post-acute infection syndromes, Long/Post-COVID condition is highly complex (7). Studies report a large variety of up to over 200 symptoms (8–10). Among the most prevalent symptoms are fatigue, headaches, attention disorder, dyspnea and hair loss (9, 11).

Mental health problems are also prominent, as up to 78% of survivors develop neuropsychiatric Long/Post-COVID symptoms, most commonly symptoms of depression, anxiety, and cognitive deficits (12–14).

Current theories regarding the pathogenesis of Long/Post-COVID hypothesise processes of immune dysregulation, microbiota dysbiosis, immunological processes, blood clotting and endothelial abnormalities or dysfunctional neurological signalling (15). Sufficient scientific evidence to adequately confirm postulated pathogenetic mechanisms is still lacking.

Apart from clinical variables, several psychological factors like psychological distress, loneliness, worry, expectations associated with COVID-19 (16) or resilience (17) are significant predictors of Long/Post-COVID symptom burden. Several recent studies focus on the psychosocial perspective and emphasize it as important as potential biological factors (18, 19).

Patients’ symptom trajectory usually shows an undulated pattern. While for many symptoms decreasing prevalences are recorded over time, stable or increasing symptom prevalences have also been observed (10). Long/Post-COVID is often associated with reduced quality of life and an inability to return to work (20–22). Furthermore, the disease impact on patients’ lives often increases 6 months after the infection (10).

In addition to the impairment of the individual’s health and quality of life, these symptoms pose a general and considerable socioeconomic burden (20). In the United States alone, Long/Post-COVID has been estimated to lead to an annual loss of income of approximately 50 billion $US. The annual cost of treatment per person has been estimated to be 9000 $US (23).

Given the association between psychological variables with Long/Post-COVID symptom burden as well as the enormous impact Long/Post-COVID can have on individuals, psychological and psychosocial approaches should be an incremental component of treatment. Although isolated nonspecific psychological interventions are a part of several intervention studies (24), to our knowledge there is no existing psychotherapeutic intervention tailored specifically to the psychosocial needs of Long/Post-COVID patients.

Therefore, we developed a psychotherapeutic manual addressing psychosocial needs as well as bodily symptoms of Long/Post-COVID patients. Explicit focus is put on coping strategies, bodily-distress management, management of affective symptoms and problems regarding patients’ social life and work life. The development of the intervention is based on expert knowledge and existing manuals for short-term psychotherapeutic interventions (25–27). Besides results from data analyses of two German COVID-19-cohorts, interviews with Long/Post-COVID-patients regarding their psychosocial needs and preferences have also been incorporated in the development of this intervention.

## Objectives

The aim of the study is to develop and pilot test a newly developed manualized psychotherapeutic intervention, which addresses in particular psychosocial needs and preferences of patients suffering from Long/Post-COVID.

## Trial design

The pilot trial is conducted as a multi-centre, 2-arm (allocation ratio: 1:1), parallel group, randomised and controlled study.

## Methods: participants, interventions and outcomes

The article was written in adherence to the SPIRIT reporting guidelines (28).

A council of Long/Post-COVID patients was formed and regular meetings were held to discuss the methods especially the content of the therapeutic intervention.

### Study setting

The study is conducted at six locations across Germany, which constitute the PsyLoCo-consortium. Participating institutions are five psychosomatic university clinics in Munich (Technical University; TU), Magdeburg, Tuebingen, Ulm and Freiburg, as well as the university Halle (Saale). The latter is responsible for the overall data management and statistical analysis. Therapeutic sessions are held in all of the psychosomatic sites.

### Eligibility criteria

Eligibility criteria for participants are as follows:

*Inclusion criteria:* 1) Age ≥ 18y. 2) Previous SARS-CoV-2 infection confirmed either by a PCR-positive test result or positive self-rapid test. 3) At least one present Long/Post-COVID-symptom (persisting min. 4 weeks after initial infection). 4) Ability to provide informed consent. 5) Availability during intervention period. 6) Suitable place of residence to attend the appointments at one of the study locations.

*Exclusion criteria:* 1) Severe psychiatric disorder according to ICD-10. 2) Current suicidality. 3) Current psychotherapeutic treatment or having received psychotherapeutic treatment for Long/Post-COVID. 4) Insufficient understanding of spoken or written German.

All therapists will be psychologists or physicians with appropriate psychotherapeutic training and they will receive training in conducting the interventions according to the manual.

### Who will take informed consent?

Study participants will be informed in detail about the study. Potential effects and benefits as well as possible side effects are explained. Additionally, participants are informed about data security and their participant rights. Study personnel will then obtain written informed consent before pre-intervention assessments (t1).

### Additional consent provisions for collection and use of participant data and biological specimens

A study module investigating intraindividual changes in blood cytokines between t1 and t2 is optional. Separate informed consent will be obtained from patients who agree to participate.

## Interventions

### Explanation for the choice of comparators

Due to the randomized assignment to either the intervention group or the control group, any systematic differences and changes regarding symptom burden should be attributed to group affiliation and having received the psychotherapeutic treatment or not. As controls, a waiting list group was chosen as not offering the intervention to controls at a later time point would likely result in poor participation.

During the trial, both study groups are allowed to use regular medical care for Long/Post-COVID-symptoms, i.e. general practitioners or medical specialists (e.g. neurologists, nephrologists, cardiologists or physiotherapists). Participants who initiate psychotherapeutic treatment other than within the study intervention will be excluded.

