### Criteria for discontinuing or modifying allocated interventions

A discontinuation of treatment or modification of the intervention will be initiated if a patient suffers acute or severe symptom deterioration including suicidality. In this case appropriate treatment will be initiated. The intervention can also be terminated by the participants themselves at any point in time.

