### Relevant concomitant care permitted or prohibited during the trial

Any kind of medical care and therapy is allowed during the trial except psychotherapy (beside the study intervention).

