### Provisions for post-trial care

It is hypothesized that participants will benefit from the intervention and that Long/Post-COVID-symptoms will improve. Harm from trial participation is not expected. If applicable, participants will be supported in finding appropriate follow-up treatment such as inpatient psychosomatic treatment or outpatient psychotherapy.

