### Plans to promote participant retention and complete follow-up

Participants can terminate study participation at any time. In this case no further outcome data are collected. To ensure completion of follow-up, participants will be contacted via e-mail and reminded to fill out the questionnaire at one week and two weeks after the initial request to complete the follow-up-questionnaire. If, after three weeks, the questionnaire has not yet been completed, participants will be given a final reminder via a telephone call.

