### Methods in analysis to handle protocol non-adherence and any statistical methods to handle missing data

Both, intention-to-treat and per-protocol analysis will be conducted to assess the extent of protocol violation. Single items missing within the outcome instruments, respectively, will be imputed by median, if less than 20% of items are missing.

Therapies are planned to be held over the course of 12 weeks. In case of any cancelled appointments therapies can be prolonged for up to two weeks. Participants who drop out before session four of the intervention will be replaced. Four missed sessions will be treated as non-adherence.

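### Excluding randomised participants who start other psychotherapy conflicts, as written, with the promised intention-to-treat analysis

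*Protocol article*

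**What the plan says.** All references are to the protocol article.

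- *Explanation for the choice of comparators*: after stating that both groups may use regular medical care while the trial runs, the section ends: "Participants who initiate psychotherapeutic treatment other than within the study intervention will be excluded". No analysis set is named.
- *Relevant concomitant care permitted or prohibited during the trial*: other psychotherapy is again ruled out for the trial period. This is separate from the baseline criterion on current psychotherapy under *Eligibility criteria*.
- The analysis sets are named in the section on non-adherence and missing data, under *Statistical methods*: "Both, intention-to-treat and per-protocol analysis will be conducted to assess the extent of protocol violation".
- *Plans to promote participant retention and complete follow-up*: "Participants can terminate study participation at any time", and then "In this case no further outcome data are collected".
- *Sample size*: 60 participants per arm, with the number set by feasibility.
- *Outcomes* and *Statistical methods for primary and secondary outcomes*: feasibility is the primary outcome. The SF-12 change from t1 to t2 is compared between arms in an exploratory mixed model to obtain an effect size for the later RCT. Drop-out and adherence are analysed as feasibility results.

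**The concern.** An intention-to-treat analysis keeps participants in the arm to which they were randomised, whatever treatment they take later. A rule that removes people for something they do after randomisation works against this, particularly when the event is likely to be related to both arm and outcome.

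That is plausible here. Controls wait without study psychotherapy, and anyone in either arm who is not improving has a motive to look elsewhere. This is an inference from the design; the article reports no rates.

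Two products of the pilot are exposed. One is the effect estimate handed to the later RCT. The other is the drop-out information: how often wait-list participants start therapy elsewhere is itself something the next trial needs to know, and it would be mixed with losses imposed by the rule.

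The stated reason for running both analyses, to gauge the extent of protocol violation, is also weakened. If people who start outside therapy are missing from both sets, comparing the sets cannot show the effect of that violation.

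**Working it through.** **1. The statements side by side**

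| Question | What the article states |
|---|---|
| When does the rule apply? | During the trial, so after randomisation |
| To whom? | Both arms |
| Excluded from what? | Not stated |
| Are these people still sent t2 and t3 questionnaires? | Not stated |
| Are they in the intention-to-treat set? | Not stated; an intention-to-treat analysis is promised |
| When does outcome collection stop? | When a participant ends study participation; whether exclusion counts as this is not stated |

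Read literally, the exclusion rule removes randomised participants, and nothing in the article brings them back.

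**2. The plan's own number**

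60 + 60 = 120, and 5 sites × 24 = 120, so the sample size is internally consistent. No alpha, power, SD or drop-out rate is given, so there is no power calculation to reproduce. With everyone retained, the intention-to-treat set is 120 and this rule causes no bias.

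**3. Illustration of the possible bias (assumed inputs)**

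Let the change score have SD 1, with higher values better. Suppose a share q of an arm is removed, namely those lowest on a latent variable that has correlation ρ with the change score. The mean of those who remain then rises by

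shift(q) = ρ × φ(z_q) / (1 − q),

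where z_q is the standard normal quantile at q and φ is the normal density. The bias is shift(intervention) − shift(control). The values of q and ρ are assumptions.

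Worked example with q = 5% in the intervention arm, 20% in the control arm and ρ = 0.5:

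- intervention: 0.5 × 0.1031 / 0.95 = 0.054
- control: 0.5 × 0.2800 / 0.80 = 0.175
- bias: 0.054 − 0.175 = −0.121 SD

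| Removed, intervention | Removed, control | Bias, ρ = 0.3 | Bias, ρ = 0.5 |
|---|---|---|---|
| 5% | 5% | 0 | 0 |
| 2% | 10% | −0.044 | −0.073 |
| 5% | 15% | −0.050 | −0.083 |
| 10% | 20% | −0.046 | −0.077 |
| 5% | 20% | −0.072 | −0.121 |
| 10% | 0% | +0.058 | +0.097 |
| 15% | 5% | +0.050 | +0.083 |
| 20% | 5% | +0.072 | +0.121 |

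With ρ = 0 the bias is zero in every row. In the rows where control losses dominate, 48 to 54 controls and 54 to 59 intervention participants remain of 60 each.

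**4. Cross-check by hand**

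Removing a share p whose mean change is d below that of the rest raises the arm mean by p × d. Assume 3% of the intervention arm and 15% of controls are removed, with d = 0.5 SD. The bias is 0.03 × 0.5 − 0.15 × 0.5 = −0.06 SD, and 0.15 × 60 = 9 controls are lost. This agrees in scale with the table.

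**The case against.** The strongest reply is that the word excluded is never defined. If it means exclusion from the per-protocol set only, with follow-up continuing, the intention-to-treat analysis is intact. This stands. A reader might infer that intention-to-treat cannot be delivered at all, and the article does not support that. What it supports is a conflict as written, which a definition would remove.

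Four further inferences are tempting and should not be drawn:

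- **That questionnaires stop for everyone who leaves therapy or is excluded.** The sentence on ending data collection concerns people who end study participation. Stopping the intervention is treated separately under *Criteria for discontinuing or modifying allocated interventions*, with no statement that data collection ends. Nor is the sentence tied to the exclusion rule.
- **That deteriorating intervention patients are systematically removed.** The same discontinuation section says "In this case appropriate treatment will be initiated". It does not say that this treatment is psychotherapy or that it leads to exclusion.
- **That maintenance of effect at t3 is flattered because the plan refers patients to therapy and then drops them.** The offer that "participants will be supported in finding appropriate follow-up treatment such as inpatient psychosomatic treatment or outpatient psychotherapy" stands under *Provisions for post-trial care*, whereas the exclusion rule applies during the trial.
- **That the absence of a rule for a wholly missing t2 score is a defect.** The only imputation rule given concerns single items ("Single items missing within the outcome instruments, respectively, will be imputed by median, if less than 20% of items are missing"), but the rest may properly sit in an analysis plan or full protocol that is not shown.

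It is also fair to say that the shifts above are smaller than the sampling error. With 60 per arm, the standard error of a standardised difference is about √(2/60) = 0.18 SD. The comparison is exploratory and the primary outcome is feasibility. This lowers the severity. It does not remove the conflict, which an unseen analysis plan could not fully repair if t2 questionnaires had not been collected.

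**Conclusion.** The point holds in a limited form. The article states a post-randomisation exclusion in both arms and promises an intention-to-treat analysis, and it does not say how the two fit together. Taken literally, the rule removes randomised participants for an event plausibly related to arm and outcome.

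The effect on the t1 to t2 estimate cannot be determined from the article. Under the assumed removal rates (0% to 20% per arm) and correlations of 0.3 to 0.5, it ranges from about −0.12 SD when control losses dominate to about +0.12 SD when intervention losses dominate. It is zero when losses and selection are equal in both arms, or when removal is unrelated to outcome. None of these rates comes from the article.

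The harm would fall on the effect and drop-out estimates used to plan the later RCT, not on a confirmatory test. The passages should be reconciled, but this is not a flaw that invalidates the pilot.

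**What to change.** Reconcile *Explanation for the choice of comparators* with the section on non-adherence and missing data by stating that:

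- participants who start other psychotherapy during the trial stay in the intention-to-treat set, in the arm to which they were randomised;
- they are left out only of the per-protocol set;
- they are still sent the t2 and t3 questionnaires;
- outside psychotherapy is recorded with its date and reported by arm.

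In *Plans to promote participant retention and complete follow-up*, state that outcome collection stops only when a participant withdraws from data collection, and that exclusion under the psychotherapy rule does not trigger it.

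The cost is small: a few sentences and one recorded item, since the questionnaires are already digital. Outside therapy may slightly dilute the estimated effect. If the follow-up planned to end in November 2023 has already closed, the analysis-set definition and the report by arm can still be applied to the data in hand.

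Whether outside psychotherapy is permitted, and whether such participants still receive the study therapy, is for the investigators and is not addressed here.

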### Intervention description

The psychotherapeutic intervention is based on insights from data analysis of two patient cohorts and a set of patient interviews focusing on psychosocial needs and preferences of patients suffering from Long/Post-COVID conditions. The therapeutic manual was developed in an iterative process by a team of interdisciplinary experts (i.e. clinical psychologists, psychotherapists, residents, medical specialists). Additional feedback and comments of a group of patient representatives was also implemented in the development of the intervention. The intervention will be carried out as individual therapy in 12 sessions with one session per week. The first therapeutic sessions were held mid-March 2023. The last follow-up-measures are planned end of November 2023. The 12-session intervention is divided into four modules. Module 1 focuses on coping and distress management, module 2 on somatic symptoms and pain, module 3 on chronic fatigue and affective symptoms and module 4 on stresses regarding social and work life. The psychotherapeutic manual contains treatment techniques from cognitive-behavioral, psychodynamic and systemic psychotherapeutic approaches and techniques (i.e. psychoeducation, work sheets, resource work; **Table 1**). The implementation of the manual offers a certain degree of flexibility. In addition to the components that are always carried out for each participant, there are optional components that can be applied according to individual needs.

**Table 1 T1:** Session focus and interventions for each therapeutic session.

Session	Session focus	Interventions
1	•Therapeutic relationship •Psychoeducation Long/Post-COVID	•Documentation symptoms •Documentation course of disease •Psychoeducation Long/Post-COVID
2	•Therapeutic relationship •Defining goals of therapy •Introduction relaxation techniques	•Introduction PMR •Introduction MBSR
3	•Resource work	•Resource list/case
4	•Mind-body interplay •Psychosomatic disease model	•Psychoeducation (e.g. lemon exercise) •Individual barrel model
5	•Interplay attention and bodily symptoms	•Psychoeducation •Strategies for attention re-focus
6	•Mindfulness and bodily symptoms	•Introduction mindful perception
7	•Long/Post-COVID and depressive symptoms	•Emotional triangle •Cognitive defusion
8	•Long/Post-COVID and personal values	•Activity planning according to personal values
9	•Long/Post-COVID and fatigue	•Strategies for handling of fatigue symptoms
10	•Long/Post-COVID at work	•Work anamnesis •Personal resources at work
11	•Performance expectations in the context of work	•Strategies for adjustment of expectations in the context of work
12	•Relapse prevention and feedback	•Summary of therapeutic insights •Identifying early warning signs •Identifying high risk situations

